#### Staff sample for survey

(*N* = 1200) All nursing staff (registered nurses, licensed practical nurses, and certified nursing assistants) working clinically full- or part-time with residents will be eligible irrespective of job category at each NH. Will be asked to complete an anonymous web-based electronic survey via touch screen tablet.

#### Focus group(s) sample

Two focus group sessions (one of residents and one of staff; six participants/ group), will be conducted at three selected NHs (one NH per arm) to evaluate implementation and perspectives regarding approach. Using convenience sampling, English-speaking intervention participants will be eligible to join, irrespective of gender, race, ethnicity, and physical ability.*Residents.* Residents (aged > 18) who are cognitively aware and willing to participate will be selected and consented to participate in one focus group per selected NH (total of three groups; *n* = 18 residents). Participants may have refused sensor monitoring.*Staff*. Nursing staff (aged > 18) working clinically full- or part-time with residents will be selected irrespective of job category and consented for one focus group per selected NH (3 groups; *n* = 18 nursing staff).

### Risk and challenges

This study design includes NHs with the same corporate management to ensure that the same standard-of-care protocols are in place in each NH. A major challenge for NH research is the potential for staff turnover. Using a successful strategy from our prior studies [31], we secured a written commitment that the study will continue even if there is a change in one or more of corporate administrative leaders for the NH system. We also have designed the study to be robust to staff turnover and potential staff resistance to a new repositioning schedule, by incorporating mandatory training with supplemental on-site instruction as needed and also incorporating training into the NH’s new staff orientations. Another potential challenge is staff inconsistency in implementing the repositioning protocol standard-of-care; consistency in repositioning is important to being able to subsequently demonstrate that the repositioning at the assigned interval actually occurred [33]. In fact, in practice, extended repositioning intervals already are thought to be extended beyond 2 h [34, 35] and there are longstanding concerns that nursing staff documentation may be unreliable for use as evidence of repositioning [20, 31, 36, 37]. The PM system monitoring capabilities will enable concerns about repositioning protocol compliance and documentation to be addressed via time-stamped tracking of identified position changes.

### The intervention

Elements of the intervention include a NH-wide assigned repositioning interval 2, 3, or 4-h) with repositioning of residents using viable VE mattresses. Monitoring and documentation of repositioning intervention will be accomplished with use of a PM system. Table 1 describes the protocol components in detail.

**Table 1 Tab1:** Protocol for implementation of intervention approach

Protocol Components	Rationale/Outcome	Persons Responsible	Time (Fig. 4)
(1) PrU Prevention and Study Protocol Education Content: Introduces all NH nursing staff to PrU etiology, evidence-based PrU prevention practices, benefits of repositioning, & EMR documentation. Outlines roles & responsibilities, staff work flow, & performance & documentation of movement of residents. Content includes NH-wide repositioning strategy & suggestions for best practice implementation with cueing every 2, 3, or 4 h (24 h/day, 7 days/wk) depending on NH’s hourly protocol. Delivery Strategies: • Researcher leads initial session containing videos embedded in PowerPoint overview with simulation of repositioning & documentation process, followed by questions & answers. • Reference cards provided to all staff summarizing PrU etiology & staff responsibilities in relation to study protocol, day-to-day procedures, & directions for carrying out the protocol & completing study measures & documentation.	Establish knowledge of PrU etiology prevention practices, & study protocol. Facilitate consistency in response to intervention protocols, safety, & group effectiveness. Encourage problem-centered thinking & learning by demonstration and return demonstration.	RNs, LPNs, NAs, NPs	Initial session week prior to repositioning protocol start; for new staff orientation: one 60-min session followed by one-on-one training as needed when working.
(2) Champion Training Champion Training Class: Champions will learn to facilitate the educational component & practice mentoring on study strategy, problem-solving about protocol implementation, EMR documentation, & observation checklist completion; Leaf sensor placement with system activation check & skin monitoring. Support by Research Facilitators: A researcher will contact each champion every week via phone or videoconferencing during the intervention for support, advising, or refreshers as needed; champions will also have a phone number to call to seek help from research staff as needed.	Prepare champions to mentor staff, build trust, maintain consistency, and facilitate sustained implementation.	Volunteer nursing staff	Week prior to repositioning protocol start: one 60-min session.
(3) Patient Monitoring System Training Focus is on patient monitoring, responding to the 2-, 3-, or 4-h visual cues on the screen displays located at nursing station and in hallway on clinical unit, and review sample data feedback & practice interpretation. Placement of Sensor on Resident: Focus is on licensed nurse & process for sensor placement and oversight of CNA routine observation. Staff will learn to place sensor and ensure its activation and to remove and discharge sensor. Leaf placement will be periodically checked by champions to ensure fidelity.	Staff will be prepared to monitor the screen display for repositioning status (cue & next repositioning times) and to complete the appropriate documentation.	RNs, LPNs, NAs, NPs	Week prior to repositioning protocol start: Part of PrU Prevention Protocol & Education session followed by one-on-one on-the-job training as needed.
(4) VE Support Surface Audit This will be completed at each NH site according to NH system’s policy. Each NH will provide audit documentation demonstrating that all mattresses are adequate and have been examined (those that were not adequate were replaced) within the last year according to NH system’s Mattress and Safety Audit Guidelines.	Ensure viable mattresses in use prior to intervention start	Research team and NH staff	Minimum of 1 month prior to repositioning protocol start.

#### Repositioning protocol

Residents who are in bed will be repositioned according to the predetermined NH-wide assigned repositioning interval of every 2, 3, or 4 h, and rotated from side to back to side. In accordance with International PrU prevention guidelines [13], residents will be positioned in the lateral position at no more than a 30^0^ tilt. While in the supine position, the head of the bed may be elevated during feeding, but the duration of elevation greater than 30^0^ will be limited to avoid exposure to friction and shear. Residents will wear pressure reduction boots if ordered by the NH; however, because there is no evidence that these perform better than elevating the heels using a pillow, the latter will be standard procedure in this study. According to NH policy, there is a standing order that nursing staff should assist non-bedfast residents while in the chair to stand/move/reposition each hour to relieve ischial pressure, preventive seating cushions will be used as necessary according to NH guidelines. PrUs resulting from sitting will appear on ischial tuberosities; these PrUs are clearly different from PrUs on the sacrum/coccyx, trochanter, and heels that occur when lying in bed. Repositioning devices (e.g., turning sheets or trapeze) will be used as appropriate to reduce friction and shear, and pillows and foam wedges will be used to maintain position according to international guidelines.

In NHs, up to 9% of long-stay residents spend the majority of most days in bed or in a chair in their room [38]. Bates-Jensen et al. found that most residents spent 17 h a day in bed [34]. We expect, however, that 90% of residents will be sitting for at least part of the day. Repositioning will occur during the time that residents are in bed. Figure 2 is a visual depicting the required assessment and repositioning safety and skin care check to be performed by nursing staff and the criteria that must be met at each decision point in implementing the repositioning protocol.

**Fig. 2 Fig2:**
[figure not shown]
Repositioning and skin safety decision tree

#### VE support surface

All NH’s VE support surfaces (mattresses) in this study will meet or exceed international guidelines [39] for the minimum acceptable requirements for density and support to ensure that a resident’s mattress is flexible enough to deflect pressure over bony areas that come in contact with the mattress. VE surfaces will be examined 2 months prior to each NH’s intervention and all mattresses that are not viable will be replaced prior to study implementation.

#### The patient monitoring (PM) system

A wireless system for monitoring resident position and movement will be used to ***visually*** cue nursing staff on electronic display screens to ensure protocol adherence and to evaluate NH-repositioning protocol delivery fidelity [40]. This system is used in hospitals and NHs to enable caregivers to implement individualized repositioning protocols and it drives compliance with the care plan by visually notifying staff when repositioning is required [7, 41, 42]. Using a skin-sensitive medical grade adhesive backing (similar to an EKG electrode), a wireless, wearable single-patient use sensor will be placed by nursing staff on the resident’s upper chest beneath the clavicle on either the right or left side at approximately the midclavicular line (at least 4 in. away from a pacemaker or implantable cardioverter-defibrillator). The individual sensor has no on- or off-switch and activates automatically when the opaque backing is removed to expose the sensor to light. Each sensor will be associated with a specific resident, will have individualized repositioning parameters such as the 2-, 3-, or 4-h interval, and will track and indicate changes in body position. The PM system’s turn management software displays each resident’s repositioning history and current positional status in an organized and simple way on strategically placed display screens at the nursing station and mid-point in each hallway, making staff aware when repositioning actions are becoming necessary or are overdue.

### Treatment fidelity

Our treatment fidelity protocols use the National Institutes of Health Behavior Change Consortium’s [43] model. To ensure intervention integrity, repositioning of residents will be assigned to and performed by nursing staff. Each resident’s repositioning activity will be monitored with a wireless sensor and documented within the PM system, and randomly scheduled weekly observation will be conducted of staff turning/repositioning selected residents (6 per week x a minimum of 4 weeks) to provide a fidelity check of the system’s accurate detection of turning/repositioning activities. Studies and clinical data show that the device effectively detects position changes according to threshold parameters, like degree or angle of position change [44, 45]. Each NH will use a single NH-wide repositioning interval as the standard of care for low-, moderate-, and high-risk residents. This pragmatic approach offers a unique opportunity to study a single NH’s facility-wide repositioning schedule, thus avoiding the potential for staff confusion if more than one schedule is executed within a facility. Furthermore, each repositioning interval will be tested in three NHs using VE surfaces, enabling replication of findings.

### Data collection & storage (see Fig. 3 and Table 2)

#### Quantitative data collection procedures

##### NH-level data.

NH Company has agreed to provide each participating NH’s characteristics, including bed size and nursing staff hours, facility-level data (PrU period prevalence and incidence, staff number, mix, and turnover) at baseline (12 months prior) and during the intervention period. Staff mix, wage, and fringe benefit rates will be also be obtained. Data will be collected from publicly available sources (https://www.medicare.gov/nursinghomecompare/search.html). These data will be used as covariates in the multivariate analyses.

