## Methods

The TEAM-UP study is a cluster randomized clinical trial with facility-level use of an assigned repositioning interval as the primary intervention and will be conducted at 9 NHs that are all using VE support surfaces. Each participating NH will be randomly assigned to one of three intervention arms. Each arm will have 3 NHs with each NH using a single, NH-wide repositioning interval at either 2, 3, or 4 h as standard of care during the 4-week intervention period. Randomization will occur at the facility level. The sequence in which the repositioning intervals are to be implemented will be randomly ordered and, then assigned to NHs inclusive of each arm of NHs. Thus, 3 clusters of 3 NHs are created with randomly sequenced repositioning intervals.

A secondary cluster is created within each NH as the NH implements its standard risk assessment protocol; residents will be clinically categorized forming clusters by level of risk for developing a new PrU. Level of risk categorization into 3 groups is defined by a Braden score of low (15–18), moderate (13–14), or high (10–12) [32]. All eligible residents will wear a wireless triaxial accelerometer sensor throughout the intervention as part of the NH’s standard of care. Residents may refuse the sensor and can decline to move when prompted by staff as part of their right to refuse care (see Fig. 1). This pragmatic approach offers a unique opportunity to study a single NH-wide repositioning schedule, thus avoiding the potential for staff confusion associated with resident-level random assignment to repositioning intervals, which would require staff to simultaneously execute multiple turning schedules.

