**Fig. 3 Fig3:**
[figure not shown]
TEAM UP study high-level components diagram and key data sources

**Table 2 Tab2:** Summary of concepts and instruments / measurements used to collect data

Concept Measured	Measures / Instrumentation	Source (Fig. 3)
Cumulative incidence of (new) PrUs for pre-intervention (baseline) period	Cumulative Incidence rate = [(# of residents with 1 or more new PrUs during a 1-month period) ÷ (# of NH residents with 3 or more day stay)] × 100; calculated monthly to establish baseline over the 12-month period before each NH intervention begins.	• MDS 3.0 • NH self-report • EMR data extract
Cumulative incidence of (new) PrUs for intervention period	Cumulative Incidence rate = [(# of residents with 1 or more new PrUs during intervention period) ÷ (# of residents participating in intervention for 3 or more days)] × 100; calculated for the full 4-week intervention period.	• MDS 3.0 • NH self-report • EMR data extract
Braden Scale©	The Braden scale is being used per protocol by participating NHs to assess resident risk for PrUs at intervention start and weekly thereafter.	• EMR data extract
Repositioning frequency	The scheduled duration of time for a resident’s pressure exposure as reflected by the 2-, 3-, or 4-h time interval at which the resident is repositioned; each NH will be randomly assigned to one of the study’s 3 arms and will use a single NH-wide repositioning frequency.	• PMS Central Server containing Monitoring Management Software
Recorded repositioning frequency	The actual time interval at which repositioning occurs, as documented by the Leaf sensor; recorded in clock time hours and minutes, 24 h per day, from start to end of resident’s participation in the 4-week intervention. Repositioning activities of residents will be captured using the Patient Monitoring System; Admission, Discharge, Transfer (ADT) feed from NHS to Monitoring System enables a match for Study ID# to resident movement, which is required for resident tracking in the event of room change, discharge/readmission, or other events.	• PMS Central Server containing Monitoring Management Software
Repositioning protocol adherence: % agreement	Percentage of agreement between scheduled repositioning frequency and repositioning frequency recorded by wireless sensor: [(scheduled clock time - recorded clock time = # minutes difference) ÷ 60] × 100]; calculated for each resident’s repositioning episode.	• PMS Central Server containing Monitoring Management Software

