Because we will be examining PrU development from assessment to assessment, the rate of PrU incidence will be modeled as a binary outcome using repeated measures logistic regression and a specified working correlation matrix that models the correlation of responses within subjects. Full likelihood estimation methods are not appropriate for repeated measures logistic regression, so generalized estimating equations (GEEs) will be used instead with model fit assessed using the quasi-likelihood information criterion (QIC). Robust standard errors, clustered at the facility level, will be employed to account for covariance among residents within facilities over time. To test the robustness of models, we will also use non-linear mixed models using PROC GLIMMIX as another option for modeling the data (instead of GEEs using PROC GENMOD). With PROC GLIMMIX, we can use random effects to model the covariance rather than clustered standard errors. As predictors, we will include time-invariant resident characteristics, e.g., age, gender, Medicaid payer, and repositioning schedule, as well as time-varying characteristics, such as resident severity measure, risk level as determined by Braden Scale© score, staffing characteristics (e.g., number, mix, and turnover), and suggested MDS resident data elements as covariates. We may lag some time-varying resident characteristics by one assessment because we want to study the associations of repositioning time with PrU development, controlling for the starting point of the resident for that assessment interval. Interaction variables will be included in the predictor data set.

Residents without PrUs who drop out of the study after at least a three-day stay but before the conclusion of 4 weeks will be included in the analysis based on intent to treat. Residents who develop a Stage 3 or worse PrU, or deep purple discoloration, will be removed from the study per repositioning protocol, but will be considered a completed case if the ulcer developed on the coccyx, sacrum, trochanter or heel. Residents who develop ulcers on sites not thought to be influenced by bed position or limited mobility, or related to sitting, will continue to be followed for analysis, but will not be included in the NH-wide protocol.

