##### Statistical power.

According to previous research, the average PrU incidence rates range from 5.2–15%. At the time of study design, the nine NHs within the NHS were identified with the highest PrU incidence rates which averaged 9.2% (SD = 3.3%). In power analyses, we used 3.5% for PrU incidence as the expected rate for intervention since it is the highest rate found in the TURN study (for moderate-risk patients). The PrU incidence rates have been translated into an odds ratio of 0.38 (= 3.5%/9.2%) as the effect size to detect. For Aim 1, odds ratios from a logistic regression of PrU incidence rates in the three treatment arms (i.e., at 2-, 3-, and 4-h repositioning frequencies), controlling for risk level, are proposed to test the difference in PrU incidence rates between the 4-h arm and the 2-h arm as well as between the 4-h arm and the 3-h arm at 4 weeks; we are assuming that the distance between the 2-h arm and the TURN 3-h odds ratio will be larger. A sample size of *N* = 951 (*n* = 317 for each arm) will be required to detect an odds ratio of .38 with a power of 0.95 at a one-tailed significance level of α = 0.05, according to G*Power. We are using a power of 0.95 instead of the conventional power of 0.80 to ensure that we will have a smaller Type II error to test the hypothesis of no-group difference that we expect to fail to reject. We are using a one-tailed test since we are only interested in determining whether the PrU rate is higher for assigned repositioning intervals longer than the current 2-h standard practice.. For Aim 2, GEE is proposed. A sample size of *n* = 114 for each group (total *N* = 342) will be required to detect an effect size of 5.7% (= 9.2% - 3.5%) with a power of 0.80 at a one-tailed significance level of α = 0.05, using the algorithms GEESIZE developed by Dahmen, et al., on an autoregressive structure for residual correlations [48]. Since the nine NHs will be randomly assigned to the three treatment arms, risk level will be the only potential covariate to be controlled in the models, and this is already considered in the power analyses. Therefore, we will target a sample size of *N* = 951 (the larger of the two required sample sizes) for both aims while taking into account potential losses due to turnover, attrition, and exclusion criteria. While this proposed study may look like a non-inferiority or equivalence trial, we will run regular one-tailed superiority tests, because (as noted earlier) we are only interested in examining whether or not the PrU rate is higher for less frequent repositioning than for the standard 2-h repositioning. (We assume that 2-h repositioning was followed to produce the 9.2% average PrU incidence rate across our 9 study NHs, because that is the current standard of care). Also, according to Snapinn [49], non-inferiority trials have many controversial assumptions and limitations that need to be made or addressed, and that is beyond the control of our study. For incidence, it is difficult to specify a non-inferiority margin for PrU rates. Instead, we will test the hypothesis of no group-difference by examining whether the 95% confidence intervals of the odds ratios (for Aim 1) or the PrU rates (for Aim 2) of the two pairs of compared groups (e.g., 4-h arm vs. 2-h arm and 4-h arm vs. 3-h arm) overlap. If the confidence intervals do overlap, the hypothesis for no-group difference will be confirmed.

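### The NH-level data paragraph admits each home's intervention-period pressure ulcer incidence, which is the outcome, as a covariate, and conflicts with two other covariate statements

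*Protocol article*

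**What the plan says.** Three sections of the protocol article describe the covariates, and each describes a different set.

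- **NH-level data.** The company will supply home characteristics "including bed size and nursing staff hours", and "facility-level data (PrU period prevalence and incidence, staff number, mix, and turnover) at baseline (12 months prior) and during the intervention period". It adds "Staff mix, wage, and fringe benefit rates will be also be obtained" and mentions publicly available data. The paragraph closes: "These data will be used as covariates in the multivariate analyses". Nothing in it exempts the ulcer measures taken during the intervention.
- **Quantitative analyses.** The GEE and mixed models take resident characteristics, repositioning schedule and time-varying terms, among them severity and "risk level as determined by Braden Scale© score, staffing characteristics (e.g., number, mix, and turnover), and suggested MDS resident data elements as covariates". Home ulcer incidence, ulcer prevalence, bed size and wages are not named, but the lists are illustrative rather than closed.
- **Statistical power.** Aim 1 is a logistic regression on the three arms controlling for risk level. Because homes are randomised, "risk level will be the only potential covariate to be controlled in the models".

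Table 2 defines incidence in the intervention period as residents with at least one new ulcer divided by residents participating for three days or more, "calculated for the full 4-week intervention period". That is the trial outcome. On the design, Methods states: "Each arm will have 3 NHs with each NH using a single, NH-wide repositioning interval".

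**The concern.** A home's ulcer incidence during the four weeks is the average of the outcome over the residents being analysed. It is measured after randomisation, and any effect of the repositioning interval passes straight through it. Adjusting for it asks whether arms differ among homes with the same result, and the answer is close to no whatever the truth.

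The direction of this bias matters here. The trial expects to find no difference and treats overlapping confidence intervals as confirming it (Quantitative analyses, Statistical power). A covariate that pulls the arm effect to the null therefore favours the expected conclusion.

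The second problem is number. The arm effect is estimated from nine homes, and the NH-level data paragraph offers at least seven home-level items, most of them at two time points. With three incompatible lists in print, the choice among them could also be made after results are seen.

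**Working it through.** The plan gives no figure of its own on this point. The checks use its design and its two planning rates.

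**1. Home-level degrees of freedom.** There are 9 homes in 3 arms. The intercept and two arm terms use 3, leaving 9 − 3 = 6.

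**2. Number of terms listed.** Bed size, nursing staff hours, ulcer prevalence, ulcer incidence, staff number, staff mix and turnover make 7. Wage and fringe rates make 9, before public data and before counting the second time point.

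**3. Rank of the home-level design (4-h versus 2-h contrast).**

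| Home-constant covariates | Weekly-varying covariates | Parameters | Rank | Result |
|---|---|---|---|---|
| 0 | 0 | 3 | 3 | estimable, 6 df left |
| 1 | 0 | 4 | 4 | estimable, 5 df left |
| 6 | 0 | 9 | 9 | estimable, 0 df left |
| 7 | 0 | 10 | 9 | not estimable |
| 4 | 3 | 10 | 10 | full rank, estimable |
| 7 | 3 | 13 | 12 | rank-deficient, not estimable |

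The fifth row takes staff number, mix and turnover as varying week by week (an assumption in line with Quantitative analyses) and enters each of the seven items once. The last row also enters the baseline values. Bed size, staff hours, baseline prevalence, baseline incidence and baseline staff number, mix and turnover are then seven fixed values per home, even with no intervention-period ulcer measure among them.

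**4. Effect of adjusting for the home's own incidence.** The rates are the plan's 3.5% and 9.2%. Placing 3.5% at 2 h and 9.2% at 4 h is an assumption made for illustration.

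- True odds ratio: (0.092/0.908) ÷ (0.035/0.965) = 0.1013 ÷ 0.0363 = 2.79.
- Home size: 951/9 ≈ 106 residents.
- 1000 simulated trials per setting. The between-home SD on the logit scale is assumed, since the article gives none on that scale.

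| Between-home SD (logit) | Median OR, no home incidence | Home incidence, linear | Home incidence, logit |
|---|---|---|---|
| 0 | 2.84 | 1.10 | 0.996 |
| 0.3 | 2.90 | 1.12 | 0.998 |
| 0.5 | 2.84 | 1.12 | 0.999 |

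The logit column follows from algebra. Write logit(p) = a + arm effect + b × logit(home's observed incidence). Setting a = 0, arm effect = 0 and b = 1 reproduces every home's observed rate exactly, so the fit has no use for the arm terms.

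**5. Does randomisation make home-level adjustment unnecessary?** Statistical power reports a mean of 9.2% and an SD of 3.3% for the nine homes identified at design. Taking that SD as between homes, the chance difference in baseline incidence between two arms of three homes has SD 3.3 × √(1/3 + 1/3) = 2.7 percentage points. The planned effect is 9.2 − 3.5 = 5.7 points. Randomising nine homes cannot be relied on to balance this factor.

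**The case against.** A reader might infer that the plan, as it stands, removes the Aim 1 arm effect or makes it inestimable. The documents do not support that.

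- Statistical power specifies Aim 1 as controlling for risk level and assigns GEE to Aim 2. With risk level alone, all 6 home-level degrees of freedom remain and the contrast is estimable.
- NH-level data is a data-collection paragraph. The closing sentence follows directly on the one about public sources, so its reach is uncertain. Wage and fringe rates in the same paragraph are cost inputs in Table 2, which makes a fully literal reading doubtful. The modelling section does not name home ulcer measures.

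A reader might also infer that seven covariates against nine homes is decisive by itself. It is not: with three staffing terms varying weekly and four fixed terms, the model has full rank.

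Nor is it a fault that severity and Braden change enter models after the intervention starts. Aim 2 exists to study their association with ulcer development, so there they are exposures of interest.

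These points limit the claim without removing it. The modelling lists are open, so they exclude nothing that NH-level data includes. The sentence on risk level as the sole covariate refers to the models generally and cannot be squared with the longer list in Quantitative analyses. Weekly staffing does not rescue identification once the baseline values are added as seven fixed terms.

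**Conclusion.** The point holds as a conditional one. NH-level data, taken at its word, admits the outcome at cluster level as a covariate and lists more home-level terms than nine homes support if most enter as constants. Any model that followed it would shrink the 4-h versus 2-h odds ratio from about 2.8–2.9 to 1.0–1.1, or could leave it unidentified. If Statistical power governs, the Aim 1 effect stays estimable. That the three sections conflict does not depend on any simulation.

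The size rests on the plan's two rates assigned to arms for illustration, on assumed between-home variation (the shrinkage was much the same at all three values tried), and on home incidence being computed from the residents analysed, as in Table 2. A company figure covering all residents would overlap less completely. The rank results rest on which terms are taken as constant within a home.

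**What to change.** State one covariate list and make the three sections agree with it.

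- Exclude intervention-period home ulcer incidence and prevalence from every model, and say so in NH-level data.
- For the Aim 1 arm comparison, adjust for Braden risk level at entry and, at home level, only the 12-month pre-intervention ulcer incidence. Table 2 already computes it monthly; use one summary value per home.
- Keep severity, Braden change and staffing measured after the start for the Aim 2 association models. Lagging by one assessment would not make them safe for Aim 1, because a lagged value is usually still taken after the interval began.
- Correct the Statistical power sentence that names risk level as the only covariate.

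The cost is wording; the data are already collected. The home-level covariate uses 1 of 6 degrees of freedom, leaving 5. Staffing and other home characteristics become descriptive for Aim 1.
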